**Trial registration number:**

ISRCTN81218533, trial protocol V.3.1 (25 January 2024).

Strengths and limitations of this studyThe continuous ambulatory vestibular assessment (CAVA) system is novel in that it records horizontal and vertical eye movements and head accelerations 24/7 and analysis of these signals when they correspond to dizziness symptoms will allow clinicians to retrospectively evaluate the attacks through review of the data.A large number of subjects recruited from centres all over the country will enable the collection of a considerable amount of data for training an artificial intelligence system to diagnose the three conditions listed.The device is technically reliable, comfortable to wear and easy to apply and remove.The CAVA system relies on the patient experiencing an episode of dizziness while wearing the device.The trial is limited to the diagnosis of the three index conditions: Ménière’s disease, vestibular migraine and benign paroxysmal positional vertigo.

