The relationship between balance and eye movements known as the vestibulo-ocular reflex stabilises images on the retina during head movement. When a malfunction occurs in the pathway involving the ears, eyes and brain, an abnormal eye movement is produced, known as nystagmus.^7^ This is characterised by drifting of the eyes in one direction followed by a corrective rapid flick of the eyes in the opposite direction. Different diseases produce different patterns of nystagmus, for example, predominantly horizontal (peripheral vestibular nystagmus), predominantly torsional (BPPV), predominantly vertical (causes outside the peripheral vestibular system).^8^,^10^ The ability to characterise nystagmus will allow us to differentiate between the various vestibular causes of a ‘dizzy attack’ and in the future may provide insights into mechanisms underlying other disorders.

CAVA (continuous ambulatory vestibular assessment) is a wearable device developed to detect nystagmus. As some dizziness can be provoked by the movement of the head,^11^ the CAVA device also records the movement of the head in three axes. The eye movement data captured by the CAVA device is a critical parameter for assessing patients with dizziness.

The CAVA system was evaluated during a clinical investigation involving 17 healthy volunteers. Algorithms were developed to detect physiologically induced nystagmus and achieved an extremely high degree of sensitivity and specificity.^12^ The device was technically reliable, patients were happy to wear it and it was safe.^13^ Participants found the device to be easy to apply and remove and found it to be comfortable to wear. They had little difficulty sleeping while wearing the device and reported that it did not interfere greatly with their daily activities. They did not feel self-conscious wearing the device. From the initial proof-of-concept prototypes, the CAVA device was designed and confirmed to record maximum ocular excursions and eye movements as small as 5 degrees. These tests took place on several subjects with different head shapes, ensuring that recording was not limited by physiological differences or by placement on the face.

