### Outcomes

#### Primary outcome

The primary outcome will be nystagmus identification using the algorithm. This will be derived for each participant by comparing the actual nystagmus data and the device-derived nystagmus data. Data will be collated to calculate an overall value for sensitivity and specificity for all participants.

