### Data analysis

The device data will be downloaded by the investigator and securely backed up locally as well as uploaded to the University of East Anglia’s secure research storage for permanent (tape backup) storage. The software will be used to convert the data from its encoded form on the SD card into the waveform samples provided by the device. The signals will then be resegmented into files, each file containing a full calendar day.

To train the algorithms, we require a collection of nystagmus waveform segments collected from a patient each labelled with the underlying diagnosis of the patient’s condition. The nystagmus waveforms from a patient’s data will be gathered by the computational team in two ways. First, by finding the positions of presses of the event marker in the signal and searching around these points for nystagmus-like signals; second by reading the patient’s diary entries and searching for signals at times when they have noted spells of dizziness (of course, these two conditions may often co-occur). Signals in these regions will be carefully assessed for possible evidence of nystagmus and any candidate waveforms will be copied and stored. Any relevant comments by the patient will be copied and stored with the accompanying waveforms. We will also use automatic analysis. We have already developed algorithms that can detect nystagmus-like waveforms with high accuracy and these will be used to both verify any waveforms found by the procedure above and to discover any other nystagmus events that the patient was either unaware of or had not marked.

After confirmation of nystagmus waveforms associated with the three target conditions of the study, algorithms will be built and tested to do automatic diagnosis. The most suitable computational technique for this task is machine learning (ML), sometimes known as ‘AI’. When using ML to make classifications, we aim to make maximum use of the available labelled data without falling into the trap of testing on material that is either part of the training set or is correlated with it which could lead to optimistically biased results. Hence the paradigm used here is to train on all the data except for that from a single subject and then test on that subject’s data. This procedure is repeated for each subject in turn and the average error rate and its SD are estimated. This technique is known as cross-validation.

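### As described, sensitivity can be counted only on nystagmus visible in the horizontal and vertical channels; if some BPPV attacks leave no such signal, it would be overstated and one overall value would hide this

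*Protocol article*

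**What the plan says.** The Primary outcome section defines nystagmus identification by the algorithm as follows: "This will be derived for each participant by comparing the actual nystagmus data and the device-derived nystagmus data". It then asks for one pooled result: "Data will be collated to calculate an overall value for sensitivity and specificity for all participants". The term for the actual data is not defined there.

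The Data analysis section gives the only account of how nystagmus segments are obtained. The team works from the device signal in two ways: by "finding the positions of presses of the event marker in the signal and searching around these points for nystagmus-like signals" and by "reading the patient’s diary entries and searching for signals at times when they have noted spells of dizziness". It continues: "Signals in these regions will be carefully assessed for possible evidence of nystagmus and any candidate waveforms will be copied and stored". Existing detection algorithms then verify these finds and look for further events in the same recordings.

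Two statements elsewhere bear on this. The Introduction gives examples of nystagmus patterns: "predominantly horizontal (peripheral vestibular nystagmus), predominantly torsional (BPPV), predominantly vertical (causes outside the peripheral vestibular system". The strengths and limitations box says of the CAVA system that "it records horizontal and vertical eye movements and head accelerations 24/7". No torsional channel is described anywhere in the article, and its absence is not among the listed limitations.

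The Sample size section sets its 95% sensitivity and 95% specificity targets separately for each of the three conditions, with 85 participants in each.

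**The concern.** Sensitivity is the share of true events that the index method finds, so it depends on how the true events are collected. If they are collected from the same trace that the algorithm reads, an attack that leaves nothing on the trace is neither a hit nor a miss. It drops out of the calculation.

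For two of the conditions this is a general remark about a reference that is not independent of the device. For BPPV the article itself supplies a specific reason to expect it: the component it calls predominant is not among the axes it says are recorded. A more careful, blinded or independent reading of the same trace would not recover an axis that was not recorded.

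At stake is what can be concluded for BPPV, which is one third of the planned sample (85 of 255). A high overall sensitivity could coexist with a poor chance of detecting a BPPV attack, and the planned summary would not show it.

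**Working it through.** **Inputs**

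- Sensitivity among attacks with visible nystagmus: 95%, the target in the Sample size section, used here as if it were achieved.
- Share of BPPV attacks with no usable horizontal or vertical signal, *f*: not given in the article. It is an assumption, shown from 0% to 20%.
- Ménière's disease and vestibular migraine: no unseen attacks assumed.
- Weights: equal numbers of attacks from each condition, also an assumption.

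The article gives no figure for visibility of BPPV attacks, so there is no stated value to reproduce on this point.

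**Step 1. What would be reported.** Unseen attacks are in neither numerator nor denominator, so the reported sensitivity is 95% whatever *f* is.

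**Step 2. Detection per BPPV attack, all attacks counted:** 0.95 × (1 − *f*).

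**Step 3. Pooled over the three conditions:** [0.95 + 0.95 + 0.95 × (1 − *f*)] / 3.

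| *f* | Reported | Per BPPV attack | Pooled, equal weights |
|---|---|---|---|
| 0% | 95% | 0.95 × 1.00 = 95% | 2.850 / 3 = 95% |
| 10% | 95% | 0.95 × 0.90 = 85.5%, about 86% | (1.90 + 0.855) / 3 = 91.8%, about 92% |
| 20% | 95% | 0.95 × 0.80 = 76% | (1.90 + 0.76) / 3 = 88.7%, about 89% |

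**Step 4. Dilution by pooling.** At *f* = 10% the gap is 95 − 85.5 = 9.5 points in BPPV but 95 − 91.8 = 3.2 points in the pooled value. Even if every attack were counted, one overall figure would show only a third of the loss. With unequal attack numbers, the pooled value is 0.95 × (1 − *wf*), where *w* is the BPPV share of all attacks.

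**Illustration.** Suppose a BPPV participant reports five attacks and nystagmus is visible, and found, in two. Labels taken from the trace give 2/2 = 100%. The yield over reported attacks is 2/5 = 40%. The second figure is not the true sensitivity, because some of the other three attacks may have had no nystagmus, but the first says nothing about them.

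**The case against.** Four points weigh against a stronger claim.

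**Predominantly is not purely.** A reader might infer that the device cannot see BPPV attacks. No section says so. BPPV nystagmus may always carry enough horizontal or vertical movement to register. The Introduction also reports proof-of-concept work in which the target diseases were differentiated from CAVA data by five parameters, none of them torsion or plane. This stands, and it is why *f* may be zero. It does not settle the matter: the article gives no proportion of BPPV attacks captured and says that consistency in a larger group remains to be shown. Nor should the Introduction be read as separating all three conditions by plane: it names a plane for BPPV but not specifically for Ménière's disease or vestibular migraine.

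**The reference is undefined rather than defined badly.** The search of the trace is introduced as a way to obtain training data, and a statistical analysis plan is to follow. Using those labels as the actual nystagmus is the likely reading, not a stated one. This also stands, but no other source is described.

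**Exclusion of participants is not established.** A reader might infer that BPPV participants with vertigo but no visible nystagmus are replaced, leaving a selected group. The Recruitment and screening section joins 30 days of data and a qualifying attack with nystagmus by and/or, and the Retention section counts a qualifying dizziness event without mentioning nystagmus. The text leaves this open.

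**Reported attacks are not a reference standard.** The article itself calls symptom reporting imprecise, and BPPV participants are offered a particle positioning manoeuvre after 4 days of wear, so later dizziness need not be accompanied by BPPV nystagmus. A proportion over reported attacks is therefore a detection yield, not sensitivity. This is accepted and shapes the fix.

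**Conclusion.** The point holds conditionally. By the article's own description, the predominant component of BPPV nystagmus is not among the recorded axes, and the only described labels come from the recorded axes. If some BPPV attacks leave no usable signal, the primary sensitivity would be overstated, and the overall value would dilute what little of this could be seen.

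The documents do not show that such attacks occur or how often. An assumed unseen share of 10% to 20% would lower detection per BPPV attack by 9.5 to 19 points, and the equally weighted pooled value by about 3 to 6 points. At a share of zero there is no bias. These figures rest on the assumed share, 95% sensitivity for visible nystagmus, no loss in the other two conditions, equal attack numbers, and the trace-based labels serving as the reference.

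The planned summary could not distinguish these cases, whereas data already being collected would help to do so. That makes this a worthwhile, inexpensive improvement, not evidence that the result will be wrong.

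**What to change.** In the Primary outcome section, and correspondingly in the statistical analysis plan:

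1. Report sensitivity and specificity by condition, in line with the Sample size section, alongside any overall value.
2. Label the sensitivity as applying to nystagmus visible in the horizontal and vertical channels.
3. Add, by condition, the proportion of all marker- or diary-reported vertigo attacks during device wear in which nystagmus was detected. Call it detection yield. It is a lower bound on sensitivity for the reported attacks, provided the detections are genuine, because some of those attacks may have had no nystagmus.
4. Show BPPV attacks before and after the particle positioning manoeuvre separately in that table.
5. State the lack of a described torsional channel as a limit on the BPPV claim.

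The cost is some rewording and one extra table from marker, diary and device data already collected. The downside is a possibly less favourable BPPV figure, which needs its label so that it is not read as sensitivity.

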#### Secondary outcomes

Secondary outcomes include safety events, device compliance, health economics, commercialisation, average time to first dizzy attack, patient acceptability and device malfunctions.

Device compliance will be calculated for each participant by appraising the percentage of time the device was worn for each day of the trial as well as for the entire 30-day trial. Data will be collated to calculate an overall value for device compliance for all participants.

The health economic study will inform the market access plan which will be produced after the study detailing any of CAVA’s financial and other patient benefits to inform the route to its commercialisation. This will be developed using study outputs as well as data from consultation with stakeholders regarding the feasibility of adoption within the NHS, patient and public (PPI) meetings and public dissemination events.

Patient acceptability will be assessed through the use of a bespoke questionnaire, completed by participants at the end of their time in the trial.

Device malfunctions will be recorded, both participant-reported (and perceived) and those noted by the clinical or data analysis teams.

Safety events (adverse events) will be reported by participants and recorded throughout the trial.

### Sample size

A minimum sample size of 85 participants for each of the three conditions is required to demonstrate a minimum diagnostic sensitivity of 95% and a specificity of 95% with a 3% margin of error for each condition.

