### Recruitment and screening

255 participants, 85 per target disease, will be recruited from ENT departments, audiology departments and departments of audiovestibular medicine through NHS hospitals. Up to a total of 400 participants may be recruited in order that up to 30 days of data (and/or at least one qualifying dizziness attack with nystagmus) from the device is collected from 255 individuals.

Potential participants will be identified by staff familiar with the trial and the relevant departments in NHS institutions in the UK. Posters will also be used to inform participants of the trial.

Potential participants will be provided with study information either in person or by post/email. They may also be contacted by phone or they may contact the clinical research team directly. All potential participants will be offered the opportunity to discuss the advantages and disadvantages of study participation with a member of the research team and/or their physician before providing consent. See online supplemental materials for a copy of the participant consent form.

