### Retention

The trial intervention period is relatively short, so retention is not expected to be too challenging. It is anticipated that some participants will not wear the CAVA device or have a dizziness attack while wearing the device within 30 days, so the sample size is inflated to allow for this. Some non-conformance will be apparent or self-reported by the participant, others will only be detected once the data is downloaded at the end of the 30 days. Therefore, recruitment will continue until the device data analysis team confirms 255 participants with one qualifying dizziness event or the maximum upper approved limit of 400 participants is reached.

A potential challenge with retention is participants who drop out not returning the CAVA device. As this could impact the rest of the trial, participants are offered a £20 voucher incentive on return of the device and electrodes.

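### 85 participants per condition give a margin of about 4.6 points at 95% sensitivity, not the stated 3 points

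*Protocol article*

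**What the plan says.** The only justification of the trial's size is one sentence in the protocol article, Sample size. "A minimum sample size of 85 participants for each of the three conditions is required", it begins, and the purpose follows: 85 per condition "is required to demonstrate a minimum diagnostic sensitivity of 95% and a specificity of 95% with a 3% margin of error for each condition". It fixes four things: the number (85), the accuracy (95% for both measures), the margin (3%) and the scope (each condition). It gives no confidence level, formula or other expected value.

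Two other sections build on the figure. Recruitment and screening sets the total: "255 participants, 85 per target disease, will be recruited", with up to 400 allowed. Retention sets the stopping point: "recruitment will continue until the device data analysis team confirms 255 participants with one qualifying dizziness event", or the cap of 400 is reached. So 85 per condition is meant as the evaluable number after losses.

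The Primary outcome section describes a pooled result: "Data will be collated to calculate an overall value for sensitivity and specificity for all participants".

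**The concern.** At 95% accuracy, 85 people look too few for a margin of 3 points at any usual confidence level. This matters because the sentence is the article's only precision target, and it drives both the total of 255 and the point at which recruitment stops. The primary objective is to tell three conditions apart, so readers will rely on the precision within each condition. Someone taking the sentence at face value would expect an observed sensitivity of 95% to carry an interval of about 92% to 98%.

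The promise to demonstrate a minimum of 95% raises a further difficulty. If 95% is both the expected value and the floor, an interval centred on it always extends below the floor, so a result exactly as planned could not support the planned claim.

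**Working it through.** **Inputs**

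- Cases per condition: 85 (Sample size).
- Non-cases per condition: 255 − 85 = 170 (total from Recruitment and screening).
- Accuracy p = 0.95, so p(1 − p) = 0.95 × 0.05 = 0.0475 (Sample size).
- Margin d = 0.03, for each condition (Sample size).
- Confidence level: not stated. Two-sided 95% is assumed (z = 1.96), and other levels are shown.
- One independent classification per participant (assumed).

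**Step 1: try to reproduce 85**

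n = z² p(1 − p) / d² = 1.96² × 0.0475 / 0.03² = 202.75, so 203 per condition. The stated 85 is not reproduced.

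| Two-sided confidence | n needed for 95% ± 3 points |
|---|---|
| 99% | 351 |
| 95% | 203 |
| 90% (one-sided 95%) | 143 |
| 80% | 87 |

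At 95% confidence, a Wilson interval needs 215 and a continuity-type correction 235. At equal shares, 203 cases per condition means 3 × 203 = 609 in total. For specificity, 203 non-cases per condition means about 1.5 × 203 = 305 in total.

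**Step 2: the margin that the stated size gives**

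Half-width = z √(0.0475 / n), in percentage points:

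| n | Use | 95% | 90% | 80% |
|---|---|---|---|---|
| 85 | sensitivity, one condition | 4.63 | 3.89 | 3.03 |
| 170 | specificity, one condition | 3.28 | 2.75 | 2.14 |
| 255 | all participants pooled | 2.68 | 2.24 | 1.75 |
| 133 | one third of the cap of 400 | 3.70 | 3.11 | 2.42 |

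For sensitivity, 4.63 / 3 = 1.54, so the margin is 54% wider than stated. Even if all 400 allowed participants were evaluable and equally split, it would still be 3.70 points.

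Read the other way, 0.03 / √(0.0475 / 85) = 1.27, which corresponds to 79.6% confidence.

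**Step 3: intervals suited to proportions near 1**

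Two-sided 95% limits:

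| Correct | Observed | Clopper-Pearson (exact) | Wilson |
|---|---|---|---|
| 81/85 | 95.3% | 88.4% to 98.7% | 88.5% to 98.2% |
| 83/85 | 97.6% | lower limit 91.8% | lower limit 91.8% |
| 84/85 | 98.8% | lower limit 93.6% | lower limit 93.6% |
| 85/85 | 100% | lower limit 95.8% | lower limit 95.7% |

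By either method the lower limit passes 95% only at 85/85. If true sensitivity is 98%, the chance of that is 0.98^85 = 0.18.

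**The case against.** The strongest defence is that the 95% is a floor and not the expected value. With an expected 98% and a margin of 3 points, the lower limit falls at 95%, and 1.96² × 0.98 × 0.02 / 0.03² = 83.7, so 84, close to 85. At n = 85 the half-width is 2.98 points. This may well be where the figure came from. But 98% appears nowhere in the article, and the simple normal (Wald) formula is unreliable so close to 1. An observed 83/85 has an exact lower limit of 91.8%, and 84/85 one of 93.6%. The Wald limit at 84/85 would be 96.5%, and on that method the chance of success at a true 98% rises to 49%, so the statement that only 85/85 suffices depends on using exact or Wilson intervals. Those are the sounder choice here. The reading may explain the number but does not secure the floor.

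Second, the confidence level is not stated, and the article condenses a fuller clinical investigation plan. That is fair: 95% is an assumption here. But the sentence still fails at 90%, and an 80% interval would be unusual enough to need saying. The finding rests on figures that the article states, not on what it leaves out.

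Third, the primary outcome is pooled, and 255 people give 2.68 points. That supports 3 points for one overall figure. The Sample size section, however, claims it for each condition, so the pooled outcome conflicts with the claim and does not rescue it.

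Last, the article ties no hypothesis test or success criterion to the margin, and the specificity shortfall (3.28 against 3) is small. Both points stand; the main error is in sensitivity.

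**Conclusion.** The concern holds. At two-sided 95% confidence and 95% accuracy, the planned size gives 4.6 points for sensitivity and 3.3 points for specificity within each condition, against 3 points stated for both. The 3-point margin is met only by pooling all 255. Attrition does not explain the difference, because 255 is already the evaluable target.

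An observed 81/85 would leave sensitivities down to 88.4% plausible, a miss rate of 11.6% against the planned 5%. The claim to demonstrate a minimum of 95% is also unsupported, since by exact or Wilson limits it needs 85 correct out of 85.

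The exact margins depend on the assumed confidence level; the conclusion is the same at 90% and 99%. Only about 80% confidence, or an unstated expected value of 98%, comes near 85.

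**What to change.** Restate the Sample size passage and carry the same figures into the statistical analysis plan. Suggested content:

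> With 85 evaluable participants per condition and an observed accuracy of 95%, the half-width of the two-sided 95% confidence interval is about 4.6 percentage points for sensitivity (n = 85) and about 3.3 for specificity (n = 170). For an overall proportion over all 255 participants it is about 2.7.

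Also:

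- name the confidence level, the expected value behind the calculation and the interval method (exact or Wilson, given proportions near 1);
- speak of estimating sensitivity and specificity, not of demonstrating a minimum;
- if 98% with a floor of 95% was intended, say so and recalculate with an exact or Wilson method.

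The sponsor could instead confine the 3-point claim to the pooled estimate. Keeping it for each condition would need about 203 evaluable people per condition (609 in total), beyond the cap of 400.

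The restatement costs wording only, with no extra recruitment, and the stated precision becomes less favourable. It should be made before data lock, so that the precision is not revised after results are seen.

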An ML algorithm learns how to adjust automatically its parameters in such a way that it will make measurements on the waveforms that maximise the classification accuracy on the three diseases. Although it would not be obvious what these measurements are, it is possible to analyse the final ML model in such a way that we can later understand what the important criteria for distinguishing between the three diseases are. However, this process requires adequate data. If there is not enough data for the algorithm to learn the correct measurements, we can ‘help’ it by providing it with automatic measurements of features that we think may be important such as slow and fast phase velocities and amplitudes and measured nystagmus frequencies. We are in the process of incorporating these parameters.

Automatic diagnosis tests will be run periodically throughout the active stage of the project to identify potential problems in the data and to check that diagnosis accuracy continues to improve as more data becomes available. The final reported results will represent the diagnostic success rate of the project. The data should prove to be a rich source for further analysis that may considerably increase our understanding of the three target conditions and related matters.

A data validation plan will be developed to describe the downloading, storage and validation of the data in more detail and a statistical analysis plan will be finalised before analysis of the data.

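### With 85 participants per condition the trial can neither estimate 95% sensitivity to within 3 points nor, with reasonable probability, show that sensitivity is at least 95%

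*Protocol article*

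**What the plan says.** The Sample size section is one sentence. It opens with "A minimum sample size of 85 participants for each of the three conditions is required", gives the purpose as "required to demonstrate a minimum diagnostic sensitivity of 95% and a specificity of 95"%, and ends "with a 3% margin of error for each condition". It states no confidence level, null value, power or assumed true accuracy.

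The 85 is an evaluable number. Under Retention, "recruitment will continue until the device data analysis team confirms 255 participants with one qualifying dizziness event" or the upper limit is reached, and under Recruitment and screening, "Up to a total of 400 participants may be recruited".

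The analysis sections describe estimation. The primary outcome is summarised as overall sensitivity and specificity. Under Data analysis, each subject is left out in turn and "the average error rate and its SD are estimated". The same section adds that "The final reported results will represent the diagnostic success rate of the project". None of these places sets a threshold or a rule for a lower limit.

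**The concern.** The sentence joins two kinds of sizing. Demonstrating a minimum is a threshold claim: the data must make values below 95% implausible. A margin of error is a precision statement: it says how wide the interval around the estimate will be. An interval centred on 95% extends below 95% whatever its width, so precision around 95% cannot show that 95% is a minimum. The stated margin also looks too narrow for 85 participants.

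This sentence is the only justification given for the 255 participants. If it stands, an observed 81 of 85 (95.3%) could be presented as meeting the planned minimum with 3-point precision, although its exact 95% lower limit is 88.4%.

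**Working it through.** **Inputs.** From the article: 85 per condition, sensitivity and specificity 95%, margin 3 points (read as a half-width), 255 evaluable in total. Assumed: two-sided 95% confidence, an equal split of the 255, and one correct-or-incorrect result per participant, treated as independent. The denominator for specificity in each condition is then 255 − 85 = 170.

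**1. Attempt to reproduce 85.** With n = z² p(1 − p)/d², p = 0.95 and d = 0.03:

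| Confidence | n per condition |
|---|---|
| 80% | 86.7, so 87 |
| 90% | 142.8, so 143 |
| 95% | 1.96² × 0.0475/0.0009 = 202.7, so 203 |
| 99% | 350.2, so 351 |

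Only a confidence level near 80% comes close to 85, and the article does not state that level. A 3-point Wilson half-width at 95% confidence needs 215. One-sample tests of 95% against 98% (253 to 409), 92% against 95% (441 to 731) and 95% against 99% (123 to 193), at one- or two-sided 5% and 80% or 90% power, do not give 85 either. The figure is not reproduced.

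**2. Precision that 85 gives.** Half-width = 1.96 √(0.95 × 0.05/n):
- sensitivity, n = 85: ±4.6 points
- specificity, n = 170: ±3.3 points

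**3. What demonstrating a minimum would take, if it means a lower 95% limit of at least 95%.** Exact (Clopper-Pearson) lower limits for sensitivity:
- 85 of 85: 0.025^(1/85) = 95.75%, which passes
- 84 of 85: 93.6%, which fails; it also fails with a one-sided 5% limit (94.5%)

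Wilson limits agree (95.7% and 93.6%). So all 85 must be correct, and the probability per condition is p^85:

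| True sensitivity | P(85 of 85) |
|---|---|
| 97% | 7.5% |
| 98% | 18.0% |
| 99% | 42.6% |

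For 80% power, an exact one-sided 2.5% test against 95% needs about 338 per condition if the truth is 98%, and about 173 if it is 99%.

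For specificity on 170, the same rule requires 168 correct, with probability 34% at true 98% and 76% at true 99%.

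**4. Sensitivity of step 3 to the reading.**
- A Wald interval passes at 84 of 85 (lower limit 96.5%). The probability is then 49% at true 98% and 79% at true 99%.
- If the exact lower limit need only reach 92% (95 minus 3), 84 of 85 is required. The probability is 7.0% at true 95%.
- If only the observed value must reach 95%, 81 of 85 is enough. The probability is 58% at true 95%.

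**The case against.** The strongest reply is that the article describes estimation throughout, so the sentence is a loosely worded precision statement and the lower-limit rule is read into it. Much of this stands. The article states no such rule, and step 4 shows how far the probabilities move under other readings. An analysis plan is to be finalised before analysis and may set a decision rule. But the reply does not rescue the sentence: read purely as precision, 85 still gives ±4.6 points for sensitivity at 95% confidence. A later analysis plan cannot give 85 a property that it lacks.

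Three stronger readings are tempting and should be resisted.
- A reader might infer that the design is hopeless because 85 of 85 has probability 0.95^85 = 1.3% when true sensitivity is 95%. That value is the boundary of the claim, where a valid test succeeds no more often than its error rate at any sample size. With 203 per condition the figure is still only 2.4%. It is not evidence about n.
- A reader might multiply the three conditions together and conclude that success is almost impossible. The article does not require joint success; its per-condition phrase can simply mean precision in each condition. A single three-class algorithm also makes independence of the three results doubtful.
- A reader might conclude that the trial must recruit 203 per condition. That would be 3 × 203 = 609 evaluable participants, above the limit of 400 recruited, and nothing in the article makes 3 points essential.

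**Conclusion.** The point holds in two parts, both about what 85 can support for sensitivity.

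The firmer part is precision: ±4.6 points where 3 is stated, with about 203 needed per condition for 3. This rests on the conventional two-sided 95% level; at about 80% confidence 85 would nearly fit, but no level is given. For specificity the gap is small (±3.3 points).

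The second part is conditional. If demonstrating a minimum means a lower 95% limit of at least 95%, exact or Wilson limits allow no errors, and the chance of success per condition is 18% at true 98% and 43% at true 99%. The article neither states that rule nor assumes a true accuracy above 95%.

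It is an error in the stated justification and in the claim attached to it. It does not show that 85 per condition is unsuitable for an estimation study.

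**What to change.** Keep 85 per condition and rewrite the sentence as an estimation aim. For example: 85 evaluable participants per condition will be used to estimate sensitivity in each condition, expected to be about 95%, with a 95% confidence interval of about ±4.6 points; specificity, on the 170 participants without the condition, will have an interval of about ±3.3 points.

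Remove the wording about demonstrating a minimum together with the 3% margin, since correcting only one would leave the other unsupported. Add that any claim of a minimum will be judged on the lower confidence limit for each condition, not on the point estimate, and use matching wording in the analysis plan.

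The cost is one rewritten sentence, one added sentence, and a less favourable stated precision and claim. No extra participants are needed. If the sponsor does want a test against 95%, the sizing must instead state the confidence level, an assumed true value above 95% and a power; step 3 of the working shows the numbers that this implies.
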